## 8. Treatment

### 8.1 Intervention arm

Besides the standard care (see paragraph 8.2) patients in the intervention arm follow an 18-week exercise program. This program consists of high-intensity resistance and interval training. The patients will train on specialized resistance training equipment and on bicycle ergometers. Training takes place in a local physical therapy practices supervised by physical therapists. Furthermore, the physical therapist will counsel the patient to maintain an active lifestyle. A detailed training manual will be available for the physical therapist. The structure of the intervention program is shown in table 1.

#### 8.1.1 Resistance exercise

The resistance program consists of six exercises targeting the large muscle groups as follows:

1. vertical row (focusing on longissimus, biceps brachii, rhomboideus)
2. leg press (quadriceps, glutei, gastrocnemius)
3. bench press (pectoralis major, triceps)
4. pull over (pectoralis, triceps brachii, deltoideus, trapezius);
5. abdominal crunch (rectus abdominis);
6. lunge (quadriceps, glutei, hamstrings).

In some cases, one of these exercises can be replaced by an alternative exercise (for instance when the patient is not able to perform the exercises or when the appropriate exercise machine is not available in the physical therapy practice). The alternatives are described in the detailed manual.

Indirect one repetition maximum (1-RM) measurements will be performed every 4 weeks. The 1-RM is the greatest resistance that can be moved through the full range of motion in a controlled manner with good posture and this measurement will be used to guide the training: In the first 12 weeks, resistance exercises are performed at 65 to 80% of 1-RM and consist of two sets of 10 repetitions. From week 12 onwards, the emphasis shifts from muscle strength to muscle endurance involving exercise with less resistance (35-40% of 1-RM) but more (20) repetitions.

#### 8.1.2 Interval training

Interval training consists of cycling two times eight minutes, before and after the resistance exercises. The steep ramp test is performed every 4 weeks to determine the right resistance. The subject is instructed to cycle at a speed between 70 and 80 revolutions per minute (RPM), starting at a work rate of 25 Watt for 30 seconds. Hereafter the load is increased by 25 Watts every 10 seconds. The test ends if cycling speed falls below 60 RPM and the maximal short exercise capacity (the maximal workload; MSEC) is recorded. Results of the steep ramp test were described in a previous publication [32]. In the first eight weeks, those eight minutes consist of alternating 30 seconds at 65% of the MSEC and 30 seconds at 30%. From week nine onwards those eight minutes consist of alternating 30 seconds at 65% and 30 seconds at 30% of the MSEC.

#### 8.1.3 Counseling

A behavioural motivation component is included to improve compliance and to stimulate physical activity outside the exercise program in addition to and after completion of the exercise program. From week 12 onwards patients are encouraged to meet the recommendations made by the American College of Sports Medicine and the American Heart Association [33]. Specific program elements include the provision of general and motivational information, both verbally and via folders, about physical activity and the desired intensity of activity based on the Borg Scale rating perceived exertion [34]. The physiotherapist uses basic counselling techniques and instruction sheets.

Table 1. Structure of the exercise program

| Week                                                                                                           | Type of training                                           | Number of training sessions | Aim of the training                                                                                                                                                                                                                                                       |
|----------------------------------------------------------------------------------------------------------------|------------------------------------------------------------|-----------------------------|---------------------------------------------------------------------------------------------------------------------------------------------------------------------------------------------------------------------------------------------------------------------------|
| 1-12                                                                                                           | Resistance training and interval training (2 x 8 minutes). | 2x per week, 60 minutes.    | 1. improve coordination and muscle hypertrophy and hereby improving muscle force.
2. become familiar with exercise program.
3. increasing aerobic capacity.
4. overcoming the fear of physical activity.
5. increasing the pleasure in being physical active. |
| 13-18                                                                                                          | Resistance training and interval training (2 x 8 minutes). | 1 x per week, 60 minutes.   | 1. promote independence.
2. maintain muscle force.
3. improve muscle endurance.
4. improve aerobic capacity.                                                                                                                                                     |
| 1, 4, 10, 12, 18, 22                                                                                           | Counseling.                                                | 6 x 15 minutes              | 1. encourage patients to pursue an active lifestyle.
2. give information about desired intensity and duration of physical activities.
3. fill out the activity diary.                                                                                               |
| Training: 30 sessions a 60 minutes = 30 hours
Counseling: 6 sessions a 15 minutes = 1.5 hours |                                                            |                             |                                                                                                                                                                                                                                                                           |

## 8.2 Standard care (control arm)

Both the patients in the intervention arm and the patients in the control arm receive standard care. The care will vary according to doctors' and patients' preferences and cannot be standardized. However, information on physical activity/training of patients in the control arm will be obtained from the physical activity questionnaire and cost-diaries. In the Netherlands, participation in the '*Herstel&Balans*' program is possible starting at least three months after completing the cancer treatment. This rehabilitation program is based on a bio-psychosocial approach [35,36]. The program takes 3 months, during which groups of 12-16 participants visit the rehabilitation center for group-based physical rehabilitation and psycho-education. The physical rehabilitation is based on the graded activity theory and consists of supervised sessions, twice a week and is being offered at more than 50 locations in the Netherlands. The training will be mostly focused on aerobic exercise and leisure sports rather than on high intensity strength training. Currently, 10-20% of patients after SCT participate in the '*Herstel&Balans*' program. The majority of patients start with this program 6 months or longer after transplantation.

## 8.3 End of protocol treatment

Reasons for going off protocol treatment are:

- Early relapse;
- Injuries and diseases, (not) related to the assessments or exercise therapy of this study;
- incomppliance of the patient;
- Death;
- Completion of protocol.

#### 8.4 Timing and location of the investigations

Figure 1 shows the timing of the assessments. The initial screening before start of the intervention ( $t=0$ ) is crucial to identify unknown health problems, to guide exercise, analyse the physiological and muscular limitations that need to be improved by training and to determine the physical loading capacity of individual patients in concert with possible physical limitations [23].

Assessment procedures will be performed at the Academic Medical Center Amsterdam or in Rotterdam (patients Erasmus MC only) according to a detailed and standardized protocol. A physician and the researcher perform the measurements (except for the DXA scan). The assessment of cardiopulmonary fitness and muscle strength will take approximately one hour; filling out the questionnaires at  $t=0$ ,  $t=1$  and  $t=2$  will take 45 minutes (which can be done at home); filling out the cost diaries will take approximately 10-15 minutes each time.

[figure not shown]

#### 8.5 Required assessments at baseline, after treatment and during follow up

Table 2 shows when the different parameters will be assessed and below the table the associated variables or instruments are listed. The measurements are described in the following paragraph.

Table 2. Measurements at different time points

|                                                        | T0      | T1 | T2             |
|--------------------------------------------------------|---------|----|----------------|
| Clinical data                                   |         |    |                |
| Medical history                            | X       |    |                |
| Disease status and treatment               | X       | X  | X              |
| Adverse events                                         | X       | X  | X              |
| Physical tests                                  |         |    |                |
| Physical examination                       | X       | X  | X              |
| Lab tests                                  |         |    |                |
| Cardiopulmonary fitness                    | X       | X  | X              |
| Muscular strength                          | X       | X  | X              |
| Body composition and bone mineral density  | X       |    | X              |
| Questionnaires                                  |         |    |                |
| Fatigue                                    | X       | X  | X              |
| Health-related quality of life             | X       | X  | X              |
| Physical activity                         | X       | X  | X              |
| Mood disturbance                          | X       | X  | X              |
| Functioning in daily life                 | X       | X  | X              |
| Return to work                            | X       | X  | X              |
| Satisfaction with the intervention        |         | X  |                |
| cost questionnaires                       | Monthly |    | Every 3 months |

1. Date of diagnosis, subtype of disease, stage of disease, history of therapy.
2. Response to treatment, progression or relapse of disease and data on any additional treatment will be recorded from medical records.
3. Height, weight, waist and hip circumferences, four skinfolds (biceps, triceps, suprailiacal and subscapular). At T0 a physician will also look for comorbidities that might interfere with the intervention program or influence outcome.
4. Lab tests: Complete blood count (haemoglobin, platelets, WBC), only if no recent lab values (<3 weeks) are available.
5. VO2 max-test.
6. Maximal handgrip strength, chair stands test and fixed dynamometry.
7. Multidimensional Fatigue Inventory (MFI) and the Fatigue Quality List (FQL) questionnaires
8. DXA-scans.
9. EORTC Quality of Life Questionnaire C30 (EORTC QLQ-C30), the EORTC Myeloma Module (QLQ-MY20), the EORTC Chemotherapy-induced peripheral neuropathy module (QLQ-CIPN20) and the EuroQol (EQ5D).
10. PASE Questionnaire and 5-day recordings of the Actitrainer accelerometer (Actigraph, Fort Walton Beach Florida, USA). A series of questions will be used to assess pre-illness lifestyle, current attitudes towards and beliefs about exercise in general and exercising after stem cell transplantation and potential predictors of compliance with the exercise program. These questions will be asked at baseline only.
11. Hospital Anxiety and Depression Scale (HADS) questionnaire.
12. Impact on Participation and Autonomy (IPA) Questionnaire.
13. RTW-questionnaire.
14. Satisfaction questionnaire; intervention arm only.
15. Cost questionnaires will be administered on a monthly basis during the period between T0 and T1. Hereafter they will be administered once every 3 months.

## 9. Outcome measures

### 9.1 Primary outcome measures:

#### 1. Cardiopulmonary fitness

Cardiopulmonary fitness is related to the ability to perform large muscle, dynamic, moderate-to-high intensity exercise for prolonged periods. Performance of such exercise depends on the functional state of the respiratory, cardiovascular, and skeletal muscle systems.  $\text{VO}_{2\text{ max}}$  testing is well established and there are international guidelines concerning standardization and interpretation strategies [37]. This technique has been shown feasible in cancer survivors [4]. The  $\text{VO}_{2\text{ max}}$  test will be performed on a cycle ergometer and a ramp test design will be used. ECG, saturation and blood pressure will be monitored and heart rate (HR) and gas exchange variables will be recorded continuously. The test will be supervised by a physician.

By applying this test a broad range of parameters can be assessed. Among these parameters are the

- Maximal work rate (Wmax)
- Ventilation threshold (VT)
- $\text{VO}_2$  at VT ( $\text{VO}_2\text{ VT}$ )
- Maximal ventilation ( $\text{V}_E\text{ max}$ )
- Maximal respiratory frequency (f max)
- $\text{VO}_2$  at respiratory exchange ratio = 1 ( $\text{VO}_2\text{ RER } 1$ )
- HR at respiratory exchange ratio = 1 ( $\text{HR RER } 1$ )
- Maximal aerobic power ( $\text{VO}_{2\text{ max}}$ )
- Maximal HR (HRmax)
- HR at VT (HR VT)
- % Saturation of Hb with  $\text{O}_2$  (S)

Prior to the aerobic exercise test pulmonary function will be assessed at rest by measuring the forced air expiratory volume in 1 second (FEV-1), the forced vital capacity (VC), inspiratory capacity (IC) and the maximal voluntary ventilation (MVV) using a portable spirometer [38].

#### 2. Muscular strength

Muscular strength refers to the external force that can be generated by a specific muscle or muscle group. Upper extremity muscular strength will be assessed using a grip strength dynamometer and lower extremity muscular strength by the '30 s chair stands' test. In addition muscular strength of the m. quadriceps will be measured isometrically using a fixed dynamometer (Biodex System).

Maximal handgrip strength is performed three times for each hand. The mean score attained for each side will be recorded. The '30 s chair stand' test has been demonstrated to be a valid and reliable measure of proximal lower limb strength in older adults. The subject is asked to stand upright from a chair with arms folded across the chest, then to sit down again and then repeat the action at his/her own/fastest pace over a 30 s period. The final test score is the number of times that the subject rises to a full stand from the seated position with arms folded within 30 s [39]. To assess the strength of the m. quadriceps, patients will also be asked to perform three maximal voluntary knee extensions with the dominant leg at 60 degrees knee angle. The highest peak torque (Nm) of the three attempts will be used for analysis.

#### 3. Fatigue

Two self-report questionnaires will be used to assess fatigue: the Multidimensional Fatigue Inventory (MFI) and the Fatigue Quality List (FQL). The MFI is a questionnaire consisting of 20 statements for which the person has to indicate on a 0-5 scale to what extent the particular statement applies to him or her. The statement refers to aspects of fatigue experienced during the previous days. Higher scores indicate a higher degree of fatigue. This self-report instrument consists of five subscales based on different dimensions: general fatigue, physical fatigue, reduced activity, reduced motivation and mental fatigue [40,41].

The patients' perception and appraisal of experienced fatigue will be assessed with the FQL [42]. The FQL consists of 25 adjectives describing the fatigue experience, organized into 4 subscales: frustrating, exhausting, pleasant, and frightening. An exploratory hypothesis is that, even if levels of fatigue severity do not change significantly over time, the subjective experience and perceived meaning of the fatigue may change as a function of physical exercise (e.g., from frustrating to pleasant, due to attributing the symptoms of fatigue to physical exertion rather than effects of the disease or its treatment). This necessitates the use of 2 questionnaires for measuring fatigue.

## 9.2 Secondary outcome measures:

### 1. Body composition and bone mineral density

Body composition and bone mineral density will be measured using whole body dual-energy X-ray (DXA). This method has been shown to give accurate and reproducible measurements of body composition [43]. The total radiation exposure is minimal. DXA scans will be performed at the T0 and T2 time point only. Body composition will also be estimated with the use of anthropometry data (height, weight, waist and hip circumferences, and thickness of four skinfolds i.e. (biceps, triceps, suprailiacal and subscapular).

### 2. Health-related quality of life (HRQL)

The EORTC Core Quality of Life Questionnaire C30 (QLQ-C30) is a questionnaire developed to assess HRQL of cancer patients [44]. The EORTC QLQ-C30 encompasses 30 items divided in five functional scales (physical, role, emotional, cognitive, social), three symptom scales (pain, fatigue, and nausea and vomiting) and an overall QoL scale. Additional single items address other symptoms commonly experienced by cancer patients (e.g., insomnia, diarrhea, constipation, etc.). The EORTC myeloma module (QLQ-MY20) is used to receive extra information to assess HRQL in MM patients. This questionnaire measures for instance body image and future perspective and different aspects of pain [50]. Furthermore, neurotoxicity will be scored using the ZLZ-CIPN20 questionnaire, an EORTC quality of life questionnaire specifically developed to assess chemotherapy-induced peripheral neuropathy [45]. Neurotoxicity is an important side effect of chemotherapy used in this patient population (e.g. vincristin, bortezomib, cisplatin) and can hamper the ability to train these patients.

The EuroQol measures the health-related quality of life [46]. This is an important instrument for the purpose of economic evaluation (see paragraph 11.2.3).

### 3. Physical activity level

Physical activity will be measured with the PASE Questionnaire [47]. In addition physical activity will be assessed by the Actitrainer accelerometer (Actigraph, Fort Walton Beach Florida, USA). The Actigraph is able to measure accelerations from 0.05 to 2.00 G. These accelerations are scored in "counts" per minute that provide information about how long and how intensive a patient has been physically active. The epoch will be set at 60 seconds and the measurement period will include 5 days including at least one weekend day.

### 4. Mood disturbance

Mood disturbance will be assessed with the 14-item Hospital Anxiety and Depression Scale (HADS; [48]). The HADS assesses symptoms of mood disturbance, yielding separate scale scores for anxiety and depression, as well as a total score. The questionnaire has been extensively used in cancer patients and has been validated for use in the Dutch population [49].

### 5. Functioning in daily life

Functioning in daily life will be assessed with the Impact on Participation and Autonomy (IPA) Questionnaire [50]. The IPA Questionnaire consists of 32 items assessing perceived level of Participation and autonomy, organized into 5 domains: autonomy in the home, family role, autonomy outside of the home, social relations, and work and education.

#### 6. Return to work

The following indicators of return to work will be measured: (1). Time to partial and to full RTW (meaning number of calendar days between end of treatment and first day at work), (2) time to full RTW corrected for partial RTW, (3) partial and full RTW rate at T=1 and T=2. (4) Details on hours worked per week, nature of work, and return to a different job will also be recorded.

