## 5. Background

The use of high-dose chemotherapy (HDC) and autologous stem cell transplantation (SCT) has improved the outcome of hematologic malignancies such as multiple myeloma (MM) and (non-) Hodgkin's lymphoma (NHL/HL). It has become standard of care in these diseases in first line and at relapse respectively. However, the long term side effects of this treatment can have a strong negative impact on quality of life [1]. Up to 75% of patients interviewed at least twelve months post-SCT report severe and persistent fatigue, and are compromised in their ability to engage in normal physical activities [2] About 30% is not able to return to work during the course of the first two years after treatment [3]. Physical deconditioning, resulting from diminished cardiovascular and pulmonary function, reduced muscular strength and cachexia were also highly prevalent [4]. With increasing survival rates, attention should not only be focused on improving cure rates but also on improving recovery after treatment, thereby increasing long-term quality of life. Preliminary results show that exercise interventions can counter the physical deconditioning after SCT, and thus might also improve the quality of life in these patients.

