### **10.2 Protocol treatment period**

The protocol treatment period is defined as the period from the baseline measurements (T0) until 30 days of the end of treatment (T1 or until the start of another systemic anti-cancer treatment off protocol, if earlier.

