#### 11.2.2 Primary analysis

Data will be analyzed on an intention-to-treat basis: patients who have been randomized to the intervention group but for whatever reason do not start or continue with training, will be encouraged to still undergo the assessments. Additionally, a per-protocol analysis will be performed with the patients who have completed at least 75% of the training sessions. Longitudinal regression analysis will be used to assess changes in each outcome measure. The two follow-up measurements will be defined as dependent variable and multi-level analysis with three levels will be used, 1) treatment center 2) time of follow-up measurement (values corresponding with performance at  $t=1$  and  $t=2$ ); 3) individual.

Regression coefficients indicate differences between intervention and control group. Regression models will be adjusted for baseline values, age and gender. To test our hypothesis that the changes in physical fitness will mediate, in part, the beneficial effect of exercise on fatigue and quality of life, a mediation analysis will be performed using Latent variable structural equation modelling.

For *hypothesis 3* scores on the self-reported measures of mood state, physical activity and HRQL will be calculated according to existing scoring algorithms. Next multilevel longitudinal regression analyses will be conducted to assess differences in each outcome measure between intervention and control group at follow-up. Regression coefficients indicate differences between intervention and control groups.

Regression models will be adjusted for gender, age and baseline values. For *hypothesis 4* (examining the differences in return to work), we will use Kaplan Meier's and the Cox proportional hazard regression for recurrent events. The general idea behind this analysis is that the different time periods are analysed separately adjusted for the fact that the time periods within one patient are dependent. Recurrences of sick leave for any reason during follow-up will be added to the Cox proportional hazards model with the

time to event approach, in which only the transitions from sick leave to return to work are taken into account.

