### 11.2.3 Economic evaluation

This project will include an economic evaluation in collaboration with an expert in this field from the EMGO+ Institute for Health and Care Research. The aim of the economic evaluation will be to determine and compare the difference in total societal costs between the intervention and the control group and to relate these costs to the difference in effects between the two groups for the primary outcomes. The economic evaluation will be performed according to the intention-to-treat principle and from a societal perspective.

Both cost-effectiveness and cost-utility analyses will be performed. The cost-effectiveness ratios will be calculated by dividing the difference between the mean costs of the two treatment groups by the difference in the mean effects of the two treatment groups. This ratio will include the primary clinical effect measures of the trial. The cost-utility ratio will express the additional costs of the intervention per quality adjusted life year (QALY). Utilities will be measured using the EuroQol (EQ5D) at baseline, at the end of the treatment and at twelve months. The EuroQol is a health-related quality of life instrument that provides a single index of an individual's quality of life. It consists of 5 dimensions resulting in 243 possible health states [52]. The health states will be valued using Dutch tariffs.

Multiple Imputation (MI) using the Multivariate Imputation by Chained Equations (MICE) will be used to impute missing cost and effect data. Bootstrapping will be used to estimate confidence intervals around the mean differences in costs between the treatment groups. The uncertainty surrounding the cost-effectiveness and cost-utilities ratios will also be estimated using bootstrapping techniques. The bootstrapped cost-effect pairs will be used to estimate cost-effectiveness and cost-utility planes, and cost-effectiveness acceptability curves. Sensitivity analysis on the most important cost drivers will be performed in order to assess the robustness of the results.

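### Time to return to work is counted from an end of treatment that the protocol does not identify, and the hypothesis 4 model counts more than the first return that defines the outcome

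*Protocol*

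**What the plan says.** Protocol section 9.2, item 6, defines time to partial and to full return to work as "meaning number of calendar days between end of treatment and first day at work". It does not name the treatment. The same item lists the partial and full return rates at T1 and T2.

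Two other places use the phrase for T1:
- The section 10.2 that sets the time window for safety reporting: "The protocol treatment period is defined as the period from the baseline measurements (T0) until 30 days of the end of treatment (T1".
- Section 11.2.3, on when utilities are measured: "at baseline, at the end of the treatment and at twelve months".

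Two places use treatment for the cancer treatment:
- Section 5, on return to work itself: "About 30% is not able to return to work during the course of the first two years after treatment".
- Section 8.2, on when an existing rehabilitation program may be joined: "starting at least three months after completing the cancer treatment".

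For hypothesis 4, section 11.2.2 plans Kaplan-Meier curves and a Cox model for recurrent events. "Recurrences of sick leave for any reason during follow-up will be added to the Cox proportional hazards model", by an approach "in which only the transitions from sick leave to return to work are taken into account". It adds that the time periods get separate analysis, with allowance for dependence within a patient.

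**The concern.** A time-to-event outcome needs a start date that exists in both arms and does not fall after the point from which the treatments can act. Section 9.2 does not fix such a date. Two analysts could follow it faithfully and build incompatible datasets.

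The event is also unsettled. Section 9.2 ends the clock at the first day at work. Section 11.2.2 lets one patient contribute several returns, including returns from later leave unrelated to the cancer. A fall back into sick leave is never an unfavourable event in that model, while each recovery from it is a favourable one. Hypothesis 4 could then rest on a hazard ratio that is not about the first return.

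**Working it through.** The protocol gives no event count, power or hazard ratio for return to work, so there is no figure of its own to reproduce.

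**1. Origin at T1.** Inputs: an 18-week program (section 7.2), with T1 at completion of the intervention (Summary). Assumption: the program starts at T0.
- T1 is day 18 × 7 = 126 after T0.
- A return at the end of program week w has time 7w - 126. Week 1 gives -119, week 10 gives -56 and week 18 gives 0.
- If completion is taken as the last counseling session, in week 22 (Table 1), the time is 7w - 154, and week 10 gives -84.

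Returns before T1 are expected, since 9.2 reports the return rate at T1. Dropping them would remove the returns made while the program was running. It would also restrict the analysis to patients selected after randomization.

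**2. Origin at the end of cancer treatment.** For patients who start the program 6-14 weeks after transplantation (section 7.2), a return in program week 10 falls at day 42 + 70 = 112 to 98 + 70 = 168 after transplantation. Times are positive, but two problems remain.
- Section 7.3 admits patients 6-12 weeks after transplantation. It also admits patients less than 8 months after it whose radiotherapy or consolidation ended 2-6 weeks ago. For the second group, transplantation and last treatment give different origins.
- Either origin precedes randomization. Returns before entry count as outcomes although the intervention cannot affect them. The documents give no rate for these, so the dilution cannot be sized.

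**3. Pooled recurrent returns.** All rates here are assumptions. The first return is identical in both arms, with mean 35 weeks. Follow-up is 52 weeks, new leaves last 2 weeks on average, and the true first-return hazard ratio is 1.

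A hand check uses events divided by time on sick leave:
- Share with a first return: 1 - exp(-52/35) = 0.774. First-absence time: 35 × 0.774 = 27.1 weeks. Time left after the first return: 52 - 27.1 = 24.9 weeks.
- New leaves per patient at r per year: R = r × 24.9/52, which is 0.24, 0.48 and 0.72 for r = 0.5, 1.0 and 1.5. Time lost to these leaves is ignored.
- Pooled rate (0.774 + R)/(27.1 + 2R): 0.0368, 0.0447 and 0.0523 per week.
- Ratios to r = 0.5: about 1.22 and 1.42.

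The Cox model compares spells at the same duration. In simulation with thousands of patients per arm it gave somewhat smaller values:

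| New leaves per year, arm A vs arm B | Pooled hazard ratio, B vs A | Stratified by episode |
|---|---|---|
| 0.5 vs 0.5 | 1.00 to 1.02 | not needed |
| 0.5 vs 1.0 | 1.15 to 1.20 | 0.98 |
| 0.5 vs 1.5 | 1.32 to 1.33 | 1.00 |

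Ranges are over repeat runs. A ratio above 1 favours arm B, which has more sick leave. With the lower rate in the exercise arm (0.5 against 1.0 in controls), the pooled ratio for exercise was 0.84.

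Other assumptions (mean first absence 200 days, 365 days of follow-up, 4,000 per arm) gave pooled ratios of 1.30 for 2 against 1 leaves of 7 days, 1.45 for 2 against 0.5, and 1.19 for 2 against 1 leaves of 30 days. With equal rates the ratio was 1.02. First-return ratios in these runs were 0.98 to 1.06, so part of the 1.30, whose first-return ratio was 1.06, is sampling error.

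**The case against.** A reader might infer that the origin is T1. The documents do not settle that. Section 10.2 sets a safety-reporting period and 11.2.3 describes utility timing; neither defines this outcome. Where section 5 discusses return to work, treatment means the transplant treatment. Reporting the return rate at T1 also makes T1 an unlikely intended origin. The supported point is that the origin is ambiguous.

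A reader might also infer that controls have no start date. That does not follow. Table 2 lists return to work at T0, T1 and T2 without an arm limit, and only the satisfaction questionnaire is restricted to the intervention arm. Controls have a T1 visit and an end of cancer treatment. They lack an origin only if the end of the exercise program itself is meant.

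Nor does an origin before randomization favour one arm. Returns before entry are balanced in expectation, so the effect is dilution.

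Finally, one might read the recurrent-event model as always rewarding sick leave. It does not. Section 11.2.2 can be read as an analysis stratified by episode, under which the distortion disappeared in the simulation, and pooling needs unequal recurrence to do harm. A theoretical reservation stands: only patients who have already returned enter later episodes, so those comparisons are not protected by randomization. Its size has not been estimated.

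The return rates at T1 and T2 need no clock and bear on hypothesis 4, but 11.2.2 assigns that hypothesis to the time-to-event methods.

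**Conclusion.** The concern holds in a limited form. The start of the clock in 9.2 is not identified, and neither main reading serves: T1 gives times of about -126 to 0 days for returns during the program, and the end of cancer treatment starts before randomization and dilutes the contrast by an unknown amount. The analysis in 11.2.2 does not match the first-return outcome in 9.2.

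The recurrent-event distortion is conditional. It needs pooled episodes, short new spells and recurrence that differs between arms. Under assumed rates of two to three times, the hazard ratio is then about 1.2 to 1.3 in favour of the arm with more sick leave. The documents supply no recurrence rates, so the likely size in this trial is unknown.

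This affects a secondary outcome and a named hypothesis, not the primary outcomes. The figure showing assessment timing is not available and might fix T1 more closely. It would not by itself say which treatment 9.2 means.

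**What to change.** In 9.2, item 6, define time to partial and time to full return as days from randomization in both arms, among patients on sick leave from paid work at randomization.

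In 11.2.2, make time to first return (partial and full, each by Kaplan-Meier and Cox) the hypothesis 4 analysis, consistent with 9.2. Keep the recurrent-event model as a supporting analysis, stratified by episode number and reported with total days on sick leave, so that more frequent leave cannot pass for a better result.

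The cost is wording in two sections. The first day at work is already needed for the outcome, and the dates of later leave for the recurrent-event model. The downside is that the main analysis does not use later episodes or patients already back at work at randomization.
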